**Follow-Up period**

- Study visits 4a and b with psychometric assessments
- Treatment with or without mECT depending on patient’s choice regardless of randomization

## Planned treatment after End of Study Participation

Further treatments after the subject’s end of study visit should be performed according to local standard procedures at each site, chosen at the discretion of the treating psychiatrist.

## Assessments

- **Sociodemographic:** Age, sex, marital status, education (in years including: school degree (Hochschulreife/Abitur, Realschulabschluss, Hauptschulabschluss), university degree (bachelor), higher education (master, PhD)) and residence (city with 100.000 inhabitants, town with 10.000 inhabitants and rural area)
- **Medical history:**

This includes psychiatric history including number of psychotic episodes, prior treatments and concomitant psychiatric disorders, other clinically significant diseases, surgeries, previous medical procedures, smoking history, use of alcohol and other drugs, and all current medications (e.g., prescription drugs, over-the-counter drugs, herbal or homeopathic remedies, and nutritional supplements).

- **Vital signs/physical examination:** Height, weight
- **Concomitant medication:** Medication taken during subject’s enrollment will be documented.
- **AEs:**

AEs will be asked for at each contact between the responsible investigator and the subject. AEs will be reported with subject ID, start and end date, description, grading, seriousness, relatedness, action taken and outcome.

- Treatment (mECT) parameters (see section 5.1)

The following **questionnaires** will be completed by the investigator during the study visits:

- **Brief Psychiatric Rating scale (BPRS):** A 18-item rating scale to measure psychiatric symptoms such as depression, anxiety, hallucinations and unusual behavior using a seven-item Likert scale. The BPRS will be assessed by means of a clinical interview that will be recorded on video and rated by a blinded rater and unblinded raters at the sites.
- **Global Assessment of Functioning (GAF):** A numeric scale to rate the social, occupational, and psychological functioning of an individual. Scores range from 100 (extremely high functioning) to 1 (severely impaired).
- **Positive and Negative Syndrome Scale (PANSS):** A numeric scale used for measuring symptom severity of patients with schizophrenia. The subject is rated from 1 to 7 on 30 different symptoms. The total score ranges from 30 to 210.
- **Mini Mental State Examination (MMSE):** The examination will be performed to screen for cognitive impairment and associated reduction. It includes tests of orientation, attention, memory, language and visual-spatial skills. The patient can reach a maximum of 30 points (no cognitive impairments) in MMSE total score.
- **17-item Hamilton Rating Scale for Depression (HAMD):** A 17-item questionnaire used to provide an indication of depression. Items are scored on a 5-point Likert-type scale. A score of 0–7 is considered to be normal, while a score of >23 is considered severe.
- **Northoff Catatonia Rating Scale (German version) (NCRS-dv):** The NRCS-dv will be used to assess the full spectrum of catatonic symptoms. It consists of 40 items describing motor (13 items), affective (12 items) and behavioral (15 items) catatonic symptoms.

The following **self-assessment scales** will be completed by subjects digitally during the study visits under the supervision of a study team member:

- **Quality of Life Enjoyment and Satisfaction Questionnaire (Q-LES-Q-18):** The Q- LES-Q-18 is an abbreviated and validated Quality of Life Enjoyment and Satisfaction Questionnaire for patients with schizophrenia.
- **THINC-it ®:** Online-Tool for Cognitive Assessment and Measurement which includes 4 objective cognitive tests (adapted from choice reaction time, 1-back working memory task, symbol digit coding, and Trails-B) and a subjective cognitive questionnaire. Results are displayed as standard deviation from the results of healthy age-, sex- and education-matched comparison individuals. <https://progress.im/en/content/download-thinc-it%C2%AE-tool>
- **Self-Stigma of Mental Illness Scale – Short Form (SSMIS-SF):** A short form of the 40-item Self-Stigma of Mental Illness Scale consisting of 20 items.
- **Stigma-Stress-Skala:** An 8-item-scale consisting of 4 items assessing perceived harmfulness of mental health stigma and 4 items assessing perceived resources to cope with stigma, with items scored from 1 to 7. A single stress appraisal is computed by subtracting perceived resources from perceived harmfulness. A higher difference score indicates the appraisal of stigma as stressful and as exceeding personal coping resources.

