| **Primary Objective and Endpoint** | To compare after a successful series of routine electroconvulsive therapy (ECT) the overall effectiveness (time to relapse) of maintenance ECT (mECT) plus treatment as usual (TAU) versus TAU only.  Endpoint: Time to relapse (relapse defined as Brief Psychiatric Rating Scale (BPRS) ≥20% higher than individual BPRS at start of phase II at any following study visit OR any unscheduled readmission due to a worsening of psychiatric symptoms OR any unscheduled visit with an BPRS ≥20% higher than individual BPRS at start of phase II). The BPRS is evaluated by an unblinded rater at site and a blinded central rater. Readmission is decided by unblinded non-study related staff. The first relapse decision is used for analysis. |
| **Main Secondary Objectives and Endpoints** | 1. To compare side effect profile and safety between mECT plus TAU and TAU only 2. To compare psychopathological changes: mECT plus TAU versus TAU only   Endpoints:  - Number of relapse free subjects at the end of phase II  - BPRS at the end of phase II  - GAF, PANSS, HAMD, NCRS-dv, Q-LES-Q-18, SSMIS-SF, stigma-stress-scale at the end of phase II  - BPRS, GAF, PANSS, HAMD, NCRS-dv, Q-LES-Q-18,  SSMIS-SF, stigma-stress-scale at the end of follow-up  Assessment of safety:  Cognitive side effects profile (MMSE, THINC-integrated tool [THINC-it])  and safety. |
| **Study Design** | This is a multi-center, observer-blind, randomized, and actively controlled parallel-group clinical trial. |
| **Sample Size** | To be assessed for eligibility (n = 300)  To be allocated to trial (n = 140 in phase I)  To be analyzed (n = 84 randomized in phase II) |
| **Study Population** | Subjects (aged 18-65 years) with current diagnosis of schizophrenia according to Diagnostic and Statistical Manual of Mental Disorders, Fifth Edition (DSM-5), BPRS total score > 45 and history of clozapine resistant schizophrenia (CRS), which will include treatment-resistant schizophrenia with clozapine intolerance or absolute contraindications for clozapine. |

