| **Interventions** | Experimental intervention:  All included subjects will be on a stable antipsychotic drug regime for 2 weeks before inclusion. All subjects will enter phase I and will receive a full course of routine ECT while being on stable antipsychotic medication. All ECT-responders (subjects with improvement of 30% or more on BPRS will enter phase II and will be randomly assigned to the experimental intervention (mECT plus TAU) or the control intervention (TAU) which both last 28 weeks. Non-responders (subjects without improvement of at least 30 % on BPRS scale) will not enter phase II.  Control intervention:  Subjects randomized to TAU only will continue on a stable drug regime for the next 28 weeks, but will not receive mECT. The number of clinical and study visits will be identical in both arms.  Intervention per patient:  Max. 35 weeks in total including a 1-week stabilization period, max. 6  weeks of routine ECT (maximal 18 sessions), and an active intervention  period of 28 weeks (15 ECT sessions).  Follow-up period: 12 months with or without maintenance ECT as determined by patients  Experimental and / or control off label or on label in Germany:  Both are on label in Germany |
| **Number of Sites** | 14 |

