# Study Intervention

## Description of Study Intervention

**Electroconvulsive Therapy (ECT)**

ECT will be performed with right unilateral electrode placement (RUL). The stimulation dose will be six times the seizure threshold based on titration during the first session. If subjects do not show a clinical response after six treatments, electrode placement will be switched to bilateral electrode placement. Propofol or ketofol (esketamine + propofol) will be used as hypnotics. Time to stimulation will be 3-4 minutes after administration of the hypnotic. Succinylcholine will be used as a muscle relaxant in the absence of contraindicatons. Flumazenil will only be used if subjects are treated with a lorazepam equivalent dose > 4 mg/day. Glycopyrronium bromide will be used to minimize hypersalivation. Esmolol and urapidil will be used to treat postictal hypertension. Electrode placement, stimulation dose, medications used during ECT, time to stimulation, postictal suppression index, midictal amplitude, maximum sustained coherence, motor seizure duration, and EEG seizure duration will be recorded in the eCRF.

**Phase I:** All subjects receive a full course of routine ECT (max. 18 sessions; 3x/week)

**Phase II:** Subjects who are randomized to the experimental intervention group will additionally receive mECT. The maintenance ECT is administered according to a fixed schedule: Intervals will be one mECT per week for the first 6 mECTs, followed by one mECT every two weeks for 5 mECTs and then one mECT every three weeks for 4 mECTs (until week 28).

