## Period of Observation and Documentation

Adverse events (AEs) will be ascertained by the investigators using non-leading questions, noted as spontaneously reported by the subjects to the medical staff at any time during the study or observed at any of the study visit.

The observation period begins with randomization and ends with the last study visit.

AEs with a grading ≥ 2 will be documented in the subject file and in the CRF. AEs of grade 1 will not be documented in the subject file and in the CRF. If applicable, all medical diagnoses or symptoms occurring prior to the beginning of the period of observation and documentation will be recorded in the CRF as medical history.

The following general rules apply to the documentation of the AEs and SAEs: The start date of an SAE must not be earlier than that of the corresponding AE. The end date of a SAE is typically the same as that of AE. The end date of the SAE must not be later than the end date of the corresponding AE. AEs and SAEs that are ongoing at the time of death are considered not resolved or resolving.

All SAEs and their relevance for the benefit-risk assessment of the study will be evaluated continuously during the study and for the final report. All SAEs will be documented in the CRF.

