## Secondary Analyses

The number of relapse free subjects at the end of phase II will be analyzed by a mixed logistic regression model (two-sided alpha=0.05) with planned treatment, strata and BPRS at baseline as fixed effects and site as random effect in all subjects randomized (ITT).

BPRS, GAF, PANSS, HAMD, NCRS-dv, Q-LES-Q-18, SSMIS-SF and stigma-stress-scale will be categorized considering relapses and dropouts as additional categories. These will be tabulated using standard descriptive measures including number of non-missing values, mean, standard deviation, extrema and quartiles.

Furthermore, to analyze BPRS, GAF, PANSS, HAMD, NCRS-dv, Q-LES-Q-18, SSMIS-SF and stigma-stress-scale per time-point linear mixed models with the respective scale at baseline, strata and treatment as fixed effects and site as random effect will be used.

An explorative analysis will be carried out for all recruited subjects, where a logistic regression will be performed for the rate of inclusion in the randomized trial on baseline criteria. This way, subjects likely to profit from a first session of ECT can be determined based on clinical criteria.

**Safety analysis:** Frequencies of subjects experiencing at least one adverse event (AE) will be displayed according to MedDRA terminology. MMSE and THINC-it will be analyzed by group using standard descriptive measures.

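### AE enquiry is tied to contacts, and the detailed schedule gives mECT more contacts than TAU, so AE frequencies can overstate mECT harm by an amount the protocol does not allow one to judge

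*Protocol*

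**What the plan says.** The protocol describes AE ascertainment in three ways.

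- Section 6.2 (Assessments): "AEs will be asked for at each contact between the responsible investigator and the subject".
- Section 8.3 (Period of Observation and Documentation): AEs are obtained by non-leading questions, or "noted as spontaneously reported by the subjects to the medical staff at any time during the study or observed at any of the study visit". Only AEs of grade 2 or higher are documented, from randomization to the last study visit.
- Schedule of Assessment: AEs are ticked at visits 2a to 2e, 3, 4a and 4b and at unscheduled visits, and nowhere else.

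The contacts themselves come from other sections. For mECT, section 5.1 states "Intervals will be one mECT per week for the first 6 mECTs, followed by one mECT every two weeks for 5 mECTs", then four at three-week intervals up to week 28. Section 6 places visits 2a to 2e and 3 on the days of sessions 3, 6, 8, 10, 12 and 15. The Schedule puts the TAU visits in weeks 3, 6, 10, 14, 19 and 28. Against this, the Interventions row of the synopsis says that both arms will have the same number of clinical and study visits.

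For the analysis, section 9.5 plans: "Frequencies of subjects experiencing at least one adverse event (AE) will be displayed according to MedDRA terminology". The first main secondary objective in the synopsis is "To compare side effect profile and safety between mECT plus TAU and TAU only".

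**The concern.** A comparison of AE frequencies needs the arms to be asked equally often, or at least over the same look-back periods. Section 6.2 follows contacts instead, and the treatment itself generates contacts. A moderate, self-limiting event early in a long TAU gap may be forgotten by the next visit, while the same event under mECT meets an enquiry within one to three weeks. Part of any AE excess under mECT could then come from more frequent asking. Section 9.9 allows for bias from unequal observation schedules in its power calculation for relapse, but the protocol makes no such allowance for AEs. The synopsis sentence on equal visit numbers would remove the problem only if TAU contacts were arranged to match the sessions, and no section arranges them.

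**Working it through.** **1. The schedule.** From section 5.1: 6×1 + 5×2 + 4×3 = 28 weeks and 6 + 5 + 4 = 15 sessions, in weeks 1, 2, 3, 4, 5, 6, 8, 10, 12, 14, 16, 19, 22, 25 and 28. Sessions 3, 6, 8, 10, 12 and 15 fall in weeks 3, 6, 10, 14, 19 and 28, exactly the TAU visit weeks. The protocol's own figures therefore reproduce. The remaining 15 − 6 = 9 session weeks (1, 2, 4, 5, 8, 12, 16, 22, 25) have no scheduled TAU visit.

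**2. Time from onset to the next contact.** The gaps are six of 1 week, five of 2 and four of 3 under mECT, and 3, 3, 4, 4, 5 and 9 weeks under TAU. For an onset spread evenly over 28 weeks, the mean wait is Σg²/(2×28):

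- mECT: (6×1 + 5×4 + 4×9)/56 = 62/56 = 1.1 weeks
- TAU: (9 + 9 + 16 + 16 + 25 + 81)/56 = 156/56 = 2.8 weeks

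**3. Effect on recorded AEs.** The protocol gives neither an AE rate nor a recall figure, so both are assumed here. Suppose that AEs are asked for at all 15 sessions under mECT and at the six visits under TAU, that true rates are equal, and that an event is reported after a wait t with probability exp(−kt), where k = ln2/h and h is the recall half-life. The mean share captured is d = (1/28) Σ(1 − exp(−kg))/k. For h = 4 weeks, k = 0.1733:

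- mECT: (6×0.1591 + 5×0.2929 + 4×0.4054)/(0.1733×28) = 0.833
- TAU: (2×0.4054 + 2×0.5000 + 0.5796 + 0.7898)/(0.1733×28) = 0.655
- Ratio: 1.27

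**4. Effect on subjects with at least one AE.** Take a true 40% in both arms, also assumed. The recorded share is 1 − exp(−L×d), with L = −ln(0.6) = 0.511.

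| Recall half-life | Captured, mECT | Captured, TAU | Ratio of recorded AEs | Subjects with ≥1 AE, mECT v TAU |
|---|---|---|---|---|
| complete recall | 1.000 | 1.000 | 1.00 | 40.0% v 40.0% |
| 26 weeks | 0.971 | 0.930 | 1.04 | 39.1% v 37.8% |
| 12 weeks | 0.939 | 0.858 | 1.10 | 38.1% v 35.5% |
| 8 weeks | 0.911 | 0.798 | 1.14 | 37.2% v 33.5% |
| 4 weeks | 0.833 | 0.655 | 1.27 | 34.6% v 28.5% |
| 2 weeks | 0.705 | 0.471 | 1.50 | 30.2% v 21.4% |

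If both arms were asked at the same time points, the ratio would be 1.00 in every row.

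**The case against.** A reader might infer that mECT subjects are certainly asked 15 times and TAU subjects six, that the AE table therefore will overstate mECT harm, and that the loss under TAU is large. With a sharp recall cut-off of 2, 3 or 4 weeks, coverage under TAU v mECT would be 12/28 v 24/28, 18/28 v 28/28 and 22/28 v 28/28, a relative TAU loss of 50%, 36% or 21%. The documents do not support that much, for five reasons.

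- Section 6.2 speaks of contact with the responsible investigator. No section says that this person sees the subject at the nine sessions without a study visit, and the Schedule does not tick AEs there.
- The synopsis claims equal visit numbers. It does not say whether a session counts as a clinical visit. If it does, the claim conflicts with the detailed schedule. If it does not, the claim leaves the nine session-only contacts untouched.
- Unscheduled visits carry an AE tick. Section 9.9 assumes relapse of 85% under TAU and 45% under mECT before missing values, so unscheduled contacts should be commoner under TAU and act the other way.
- A cut-off of 2 to 4 weeks is an invention. Only grade 2 or higher is recorded, start and end dates are collected, and spontaneous reports count at any time. All of this favours capture over a longer interval.
- The counts of 15 and six apply to completers. At the planning hazard of 0.3433 per month, taking 28 weeks as six months, exp(−0.3433×19×6/28) = 25% of TAU subjects reach week 19, where the 9-week gap starts, without a relapse or a missing value counted as one.

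It is also fair to say that the AE display is descriptive, that MMSE and THINC-it are scheduled at identical visits in both arms, and that follow-up has the same two visits in both. What remains is that equal ascertainment is not secured by design, and that the three descriptions of AE enquiry do not agree. An analysis plan alone cannot repair this, because AE sources can be separated later only if they were recorded at the time.

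**Conclusion.** The protocol ties AE enquiry to contacts and schedules more contacts for mECT than for TAU, so the planned AE frequencies can overstate mECT harm relative to TAU. That they do so is not established. If sessions count as enquiries and true rates are equal, the ratio of recorded AEs lies between 1.00 and 1.50 over the recall assumptions tried, before the offsets named above, which cannot be quantified from the protocol. No test, sample size or primary result is affected. The point still deserves correction: comparative safety is a main secondary objective, this is the only AE comparison the protocol describes, and the remedy is cheap if made before data are collected.

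**What to change.** 1. Reconcile the synopsis (Interventions), the Schedule of Assessment and sections 6.2 and 8.3 on when AEs are asked for, and say whether an mECT session counts as such a contact.
2. In both arms, ask the same non-leading question, covering the period since the last study visit, at visits 2a to 2e, 3, 4a and 4b.
3. For each AE, record in the eCRF where it was first noted (study visit, mECT session, spontaneous or unscheduled) and whether it was reported in answer to the study-visit question, even if already recorded at a session.
4. In section 9.5, keep the full table of AEs from all sources by arm. Add a like-for-like table of AEs reported at study visits, including those first noted at a session and reported again, plus all SAEs.

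AEs first noted at sessions should not simply be dropped from the comparison. The session-day visits close gaps of only 1 + 1 + 2 + 2 + 3 + 3 = 12 of the 28 weeks. Coverage would then be 43% under mECT against 18/28 = 64% under TAU with a three-week cut-off, or 43% against 100% with complete recall. That would reverse the bias in favour of mECT.

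The cost is one or two eCRF fields, short edits to the sections named and one extra table. The like-for-like table will miss brief AEs not recalled at the next study visit, which is why the full table stays. Recording of AEs at sessions for patient safety is unchanged.

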# Discontinuation and Early Termination

Any subject can withdraw from the study intervention or the study verbally or in writing at any time without personal disadvantages and without having to give a reason. However, the investigator should make a reasonable effort to ascertain possible reasons, while fully respecting the subject's rights. Specifically, the subject must not be coerced or unduly influenced to continue participation. Any given reason should be specified in the subjects file and in the CRF.

The investigator can also discontinue the study intervention after considering the risk-to-benefit ratio, if he / she no longer considers the treatment justifiable. The date of and the primary reason for withdrawal (one primary reason must be determined), as well as the observations available at the time of withdrawal are to be specified in the CRF.

## Temporary Discontinuation from Study Intervention

The study intervention is allowed to be postponed once for at most one calendar week but not to skip one.

Visit 2 is regarded to take place in week 0, e.g. calendar week 20. For the patients receiving mECT, the first mECT should be scheduled in the next calendar week, e.g. calendar week 21, and the 3rd mECT (Visit 2a) should take place in calendar week 3 after V2, e.g. calendar week 23 and so forth. A calendar week is from Monday to Sunday.

It is allowed to postpone one mECT for at most one calendar week, e.g. if the mECT is planned in the calendar week 5, it is allowed to perform it in week 6 but neither in week 7 nor week 4. Thereafter, all mECTs have to be shifted, e.g. if the mECT is performed in week 6 instead of week 5, the next mECT has to take place in week 7. Therefore, the last mECT takes place in calendar week 29 after V2.

It is not allowed to postpone mECTs twice, so that the last mECT would take place 30 weeks after V2.

It is not allowed to receive two mECTs within one calendar week.

## Permanent Discontinuation from Study Intervention / Study

Permanent discontinuation from study intervention is any discontinuation associated with the investigator’s or the subject’s definitive decision not to re-initiate the study intervention. The following criteria will lead to a permanent discontinuation from study intervention:

- Subject’s request, i.e. withdrawal of consent,
- Loss to follow up,
- Relapse (BPRS > 120% of baseline [visit 2]) during a study visit or during an unplanned visit
- Unplanned hospitalization due to worsening psychiatric symptoms.
- The treatment is postponed more than once for at most one week or the treatment is postponed more than one week.

All subjects who discontinue the study prematurely, a withdrawal examination at least with respect to the secondary endpoint is offered at any time up to week 28 of the subject study inclusion (time of randomization, Visit 2). The subject must be asked to consent to this last examination. The (oral) consent must be documented in the patient file. The withdrawal examination must be documented in the CRF.

For details concerning sample and statistical considerations see chapter 9.

- - 1. Lost to Follow-Up

Subjects will be considered lost to follow-up if they fail to show up for study visits and cannot be contacted by the site. Site personnel is expected to make diligent attempts to contact subjects who did not show up for a scheduled visit or were otherwise not available. These contact attempts should be documented in the subject’s medical record.

